## Conclusion

In conclusion, by examining neurocognitive characteristics of rrMDD, the NEWPRIDE study will provide more insight in vulnerability to relapse and working mechanisms of psychological relapse prevention interventions. Unravelling the mechanisms of relapse prevention will improve our understanding of changes that are needed to lower an individual’s relapse vulnerability and may add to the development of more targeted and personalised interventions. Furthermore, results of the study may lead to the identification of neurocognitive predictors of both individual relapse risk and the chance that an individual might benefit from PCT, based on characteristics in the remitted phase. Finally, as routinely performing neuroimaging investigations for predicting treatment success is clinically not feasible, this study aims to validate the PDR as a marker of brain activation during emotion regulation in remitted MDD, for use in innovative non-imaging, brain-informed prediction and monitoring of PCT success.

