**Methods:**

In this randomized controlled trial, 75 remitted recurrent MDD (rrMDD) patients will be included. Detailed clinical and cognitive measurements, fMRI scanning and pupillometry will be performed at baseline and three-month follow-up. In the interval, 50 rrMDD patients will be randomized to eight sessions of PCT and 25 rrMDD patients to a waiting list. At baseline, 25 healthy control participants will be additionally included to objectify cross-sectional residual neurocognitive abnormalities in rrMDD. After 18 months, clinical assessments of relapse status are performed to investigate which therapy induced changes predict relapse in the 50 patients allocated to PCT.

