### Aims

In the Neurocognitive Working Mechanisms of the Prevention of Relapse In Depression (NEWPRIDE) study, the neurocognitive mechanisms of preventive therapy will be investigated using a within-subject longitudinal comparison of cognitive biases and fMRI characteristics related to positive and negative emotion processing before and after PCT, as compared to a waiting list control group. At baseline, a healthy control (HC) group will be included for cross-sectional comparison of residual abnormalities.

The present study has four main aims. Firstly, we aim to cross-sectionally examine whether cognitive biases and functional magnetic resonance imaging (fMRI) responses during the regulation of positive and negative emotions in medication-free, highly recurrent, remitted MDD (rrMDD) patients differ from controls. We hypothesize residual abnormalities in rrMDD patients compared to HC in (i) an amygdala-insular-subgenual anterior cingulate cortex (ACC)-ventrolateral prefrontal cortex (PFC) circuitry associated with biased processing of negative emotional information, (ii) a striatal-medial PFC circuitry associated with biased processing of positive emotional information, and (iii) the lateral-and medial PFC circuitry associated with cognitive control [75].

Secondly, this randomized controlled fMRI-study is the first to investigate the neurocognitive working mechanisms of PCT (compared to a waiting list condition) in rrMDD patients. We hypothesize that PCT will result in increased lateral and medial prefrontal activation, dampened activation of limbic regions, and improved connectivity between these regions during emotion regulation, which will coincide with normalised processing and regulation of negative information and a lowered likelihood of a prevailing negative mood. Furthermore, we hypothesize that increased PFC activation following PCT relates to increased preferential processing of positive information [70, 76].

Thirdly, we aim to identify pre-treatment neurocognitive markers predictive of long-term PCT success measured at 18-month follow-up. It is expected that low pre-treatment insular and PFC activation [39, 77] and low PFC connectivity with emotion processing areas during emotion processing predicts favourable treatment response [78]. Also, we hypothesize that participants with larger pre-post differences on neurocognitive measures, will show lowest relapse up until18-month follow-up.

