#### Randomization

Allocation sequence will be based on computer-generated random numbers. The first 50 rrMDD patients will be randomized over either the treatment condition or the waiting list control condition, to allow for instantaneous analysis of immediate PCT effects after inclusion of these participants. The 25 last included rrMDD patients will be allotted to the treatment condition, but will be given the same information (and thus hold the same expectations regarding their chance of being in the treatment condition). Patients and the principal investigators will not be blind to the treatment condition. However, to ensure unbiased assessment of clinical state and neuropsychological testing, the researchers who are involved in further assessments will be kept blind, and participants will be asked not to inform the assessor on their allotted condition.

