#### MRI data

Quality of BOLD fMRI data will be extensively checked, before data will be pre-processed according to standard recommended procedures. Subsequently, data will be modelled on the subject level using onsets/duration for the different task conditions, or time-course information. On the second level, between-group comparisons will be performed in order to analyse residual abnormalities in emotion regulation capacity, verbal working memory performance and resting state-perfusion and functional connectivity. A multilevel analysis model will be set up to test for the effects of treatment on these measures. Furthermore, linear modelling will be applied to identify and test the predictors of long-term treatment success, as defined by symptomatology (at T0, T1, T2) and relapse status and course (T1-T2) in the larger sample of remitted patients who have received therapy. Multivariate pattern analysis will be performed to evaluate the predictive value of post-treatment characteristics and pre-treatment changes for long-term treatment success. Effects will be considered significant at *p* < .05, corrected for multiple comparisons.

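### The 18-month prediction analyses use PCT-treated patients only, so they can identify predictors of relapse under PCT but not predictors of benefit from PCT

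*Protocol article*

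**What the plan says.** **What is promised.** The third aim (Aims section) is to "identify pre-treatment neurocognitive markers predictive of long-term PCT success measured at 18-month follow-up". It adds the hypothesis that "participants with larger pre-post differences on neurocognitive measures, will show lowest relapse up until18-month follow-up". The abstract's version of this aim speaks of predicting treatment effects, the pupil-dilation aim speaks of predicting PCT effects, and the Conclusion holds out "predictors of both individual relapse risk and the chance that an individual might benefit from PCT".

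**Which patients are used.** The abstract says the 18-month assessment is "to investigate which therapy induced changes predict relapse in the 50 patients allocated to PCT". The MRI data section fits the prediction models "in the larger sample of remitted patients who have received therapy". Sample size explains that the PCT group was enlarged to 50 for this purpose, and the Discussion again places success prediction in the treatment condition. The waiting list is assigned to the analysis of immediate effects, 25 vs 25, from T0 to T1.

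**How the 50 arose.** The abstract states that "50 rrMDD patients will be randomized to eight sessions of PCT and 25 rrMDD patients to a waiting list". The Randomization section says otherwise: the first 50 patients are randomised between the two conditions, and "The 25 last included rrMDD patients will be allotted to the treatment condition".

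**The concern.** Benefit from PCT is a contrast between a patient's outcome with PCT and without it. An association between a marker and relapse among treated patients contains no information on the second half of that contrast. A marker that raises relapse risk equally with and without PCT will look the same as one that identifies who responds.

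The same applies to change scores. Within the PCT arm, a patient's T0-T1 difference combines the effect of therapy with retest effects, natural course and regression to the mean. If that difference is related to relapse, the data do not show which component carries the relation.

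At stake is the interpretation of the third aim. A prognostic finding would be reported as a predictor or mechanism of treatment benefit. The Conclusion treats relapse risk and benefit as two separate things, but the planned analysis can estimate only the first.

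**Working it through.** **The plan's own figure.** The article states no power for 18-month prediction in the 50 PCT patients, so there is nothing to reproduce. Its statement on groups of 25 and moderate effects concerns other comparisons, and this point does not depend on it.

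**1. Can the PCT-only test separate prognosis from benefit?**
- From the article: 50 PCT and 25 waiting-list patients, α = 0.05, 50% relapse by 18 months.
- Assumed: standard normal marker, odds ratio (OR) of 2.0 or 2.25 per SD, two-sided Wald test in logistic regression, 50% relapse in both arms at the average marker value, no attrition. About 3,000 runs per scenario.

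| Marker | PCT-only test, n = 50 | Interaction, 50 vs 25 | Interaction, 25 vs 25 |
|---|---|---|---|
| Purely prognostic, OR 2.0 | 59.6% | 3.2% | 3.6% |
| Purely prognostic, OR 2.25 | 70.9% | 3.8% | 2.2% |
| Purely predictive, OR 2.0 | 57.2% | 25.9% | 18.0% |
| Purely predictive, OR 2.25 | 71.9% | 33.4% | 21.2% |

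The PCT-only column is nearly the same for both kinds of marker. The interaction test separates them, but with little power.

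**2. Is staying well under PCT the same as benefiting?** Sample size expects 50% relapse in remitted recurrent patients generally. The Discussion uses the same 50% for both scanner groups in the PCT prediction analysis. No separate untreated rate is given. If the untreated rate is u, and PCT never causes a relapse, the share of PCT non-relapsers who owe that outcome to PCT is (u − 0.50)/0.50. For assumed u:
- 0.50: 0%
- 0.60: 20%
- 0.70: 40%
- 0.80: 60%

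Over this range, between 40% and 100% of those who stay well would have done so anyway.

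**3. What could the randomised comparison detect?** Primary outcome measures and MRI data list IDS-SR at T1 among the outcomes for treatment predictors. For a continuous outcome in SD units and a marker with SD 1, the slope SE per arm is about 1/√n. The difference between arms detectable with 80% power at two-sided 0.05 is (1.96 + 0.84) × √(2/n).
- n = 25 per arm: 2.80 × √(2/25) = 2.80 × 0.283 = 0.79 SD per SD.
- n = 20 per arm, after the Discussion's 20% loss: 2.80 × √(2/20) = 2.80 × 0.316 = 0.89 SD per SD.

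These figures do not carry over to binary relapse. With 50% relapse and 25 vs 25, the detectable interaction is 2.80 × √(1/(25 × 0.25) + 1/(25 × 0.25)) = 2.80 × 0.566 = 1.58 log-odds per SD, a ratio of odds ratios of about 4.9.

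**4. Allocation wording.** The abstract has 50 randomised to PCT and 25 to the waiting list. Sample size and Randomization have 25 and 25 randomised, plus 25 assigned to PCT without randomisation. So 25 of the 50 patients in the prediction sample (half) were not randomised.

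**The case against.** Several counter-arguments have force.

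- **The waiting list is used.** A reader might infer that therapy-induced change is never controlled. The documents do not support that: Aims, Sample size, MRI data and Discussion all plan a comparison of T0-T1 change with the randomised waiting list. Only the step from an individual's change to relapse lacks a comparator.
- **The Conclusion is hedged.** It says what results may lead to, and its relapse-risk half is legitimate as prognosis under PCT. This stands, but the aims use benefit language without the same hedge, and the Discussion does not name the limit.
- **Harm.** A reader might infer that a marker from this trial would be used to give or withhold PCT. The article proposes no such use and speaks only of possibly helping to develop more targeted interventions.
- **Certainty.** A reader might infer that a false finding is bound to follow. It is not: a purely prognostic marker was significant in about 60% to 71% of runs, and only under assumed odds ratios.
- **The 25 non-randomised patients.** A reader might take these as the cause. They are not, since a PCT-only analysis of 50 randomised patients would have the same limit. Their allocation is disclosed in the body of the article, and the abstract's wording is a separate inconsistency.
- **A T1 interaction does not answer the 18-month question.** This stands. Patients enter with IDS-SR of 13 or less, so there is little room for improvement at three months. The design and Table 1 do not restrict T2 to PCT patients, but the article does not say what waiting-list patients receive after T1, so a clean 18-month comparator cannot be assumed.

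**Conclusion.** The concern holds as a mismatch between the question and the analysis. The 18-month analyses can show which markers and changes go with relapse among patients given PCT. They cannot show who benefits from PCT, or that an individual's change was caused by it. This follows from the design and needs no numerical assumption.

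The size depends on assumptions. At odds ratios of 2.0 to 2.25 per SD, the PCT-only test is significant in about 60% to 71% of runs for a marker unrelated to benefit, against 57% to 72% for a true effect modifier. The randomised alternative is weak, with 18% to 21% power for relapse at those values with 25 vs 25 and complete follow-up. It can support an exploratory analysis, not a firm claim. The abstract's statement on randomisation contradicts the body of the article and needs correcting in any case.

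**What to change.** 1. Reword the third aim, the abstract and the Conclusion so that 18-month associations in the 50 PCT patients are described as prognostic under PCT. Call the pre-post measure observed change rather than therapy-induced change when it is related to relapse. Name this limit in the Discussion.
2. For IDS-SR at T1, add an exploratory marker-by-arm interaction in the first 50 randomised patients. State its detectable slope difference: about 0.8 SD per SD with 25 vs 25, about 0.9 after 20% loss. Make no claim about benefit at 18 months unless T2 data from the waiting list, and what those patients received after T1, allow a randomised comparison.
3. Correct the abstract to 50 patients randomised between PCT and waiting list (25 vs 25) plus 25 non-randomised PCT patients.

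**Cost.** Changes of wording and one model term on measurements already planned. The claim becomes more modest, and the added test has low power. A comparison at 18 months would cost more, because it depends on waiting-list follow-up that the article does not describe in enough detail.

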## Data Availability

Data will be entered by two separate researchers, and anonymously stored on a shielded drive. Personal information will be stored separately in password-protected files. Only the authors have access to the final dataset. Analytical code and anonymised data will become available from the senior author on request. We will submit study results for publication in peer reviewed journals and presentation at (inter) national conferences. There are no publication restrictions. We will notify participants of publication.

## Abbreviations

ACC: anterior cingulate cortex
Ag: silver
AgCl: silver chloride
AN(C)OVA: analysis of (co)variance
ARDPEI: Attentional Response to Distal vs. Proximal Emotional Information
BOLD: blood oxygenation level dependent
BVAQ: Bermond-Vorst Alexithymia Questionnaire
CTQ: Childhood Trauma Questionnaire short form
DART: Dutch Adult Reading Test
DAS-A: Dysfunctional Attitude Scale form A
DDOPS: Domains and Dimensions of Pleasure Scale
EPI: echo planar imaging
ERQ: Emotion Regulation Questionnaire
ERT: Emotion Regulation Task
fMRI: functional magnetic resonance imaging
HAQ-II: Helping Alliance Questionnaire-II
HC: healthy control
HRV: heart rate variability
IAT: Implicit Association Task
IDS-SR: Inventory of Depressive Symptomatology – Self-Report
LARSS: Leuven Adaptation of the Rumination on Sadness Scale
LEIDS-RR: Leiden Index of Depression Sensitivity 2nd revision
MDD: Major Depressive Disorder
MDE: Major Depressive Episode
mm: millimeter(s)
MR: magnetic resonance
MRI: magnetic resonance imaging
ms: millisecond(s)
NEO-FFI: NEO Five Factor Inventory
NEWPRIDE: Neurocognitive Working Mechanisms of the Prevention of Relapse in Depression
NWO: Dutch Research Council
PANAS: Positive and Negative Affect Scale
pCASL: pseudo-continuous arterial spin labelling
PCT: Preventive Cognitive Therapy
PDR: pupil dilation response
PFC: prefrontal cortex
RC: respiration cycle
RCT: randomized controlled trial
rMDD: remitted Major Depressive Disorder
RPA: Responses to Positive Affect
rrMDD: remitted recurrent Major Depressive Disorder
RS: resting state
SCID-I: Structured Clinical Interview for DSM-IV Axis I disorders
SCR: skin conductance reactivity
T0: timepoint 0, baseline
T1: timepoint 1, 3-month follow-up
T2: timepoint 2, 18-month follow-up
TE: echo time
TR: repetition time
V: voltage
VWMT: Verbal Working Memory Task
WAIS-IV: Wechsler Adult Intelligence Scale-IV
